**Gait speed**

Gait speed will be measured using 4-metre (m) gait speed. A 4-m flat and unobstructed course will be marked out by tape. Participants will be asked to walk at their usual speed. Once the participant’s foot is across the finish line, the time taken to complete the course will be recorded
^
67,
68
^.

**Muscle strength**

Handgrip strength will be measured as an indicator of upper limb muscle strength using a dynamometer (Jamar hydraulic hand dynamometer)
^
69
^. Participants will be asked to squeeze the dynamometer handle with force, with the arm at a 90-degree angle in the seated position. Each participant will complete the test three times with each hand to get an average
^
69
^. The 2019 EWGSOP cut-offs to define low handgrip strength (<27 kg for males and <16 kg for females) will be used
^
1
^.

The Five times Sit-To-Stand (5xSTS) will be used to assess lower limb muscle strength
^
70
^. Participants will be asked to stand from the chair five times as quickly as possible and the time taken to complete the assessment will be recorded
^
70
^. Using the 2019 EWGSOP cut-off, low muscle strength will be defined as >15 seconds
^
1
^.

**Cognitive function, depression risk and activities of daily living**

Cognitive function will be measured with the Mini-Mental State Examination (MMSE)
^
49
^. Cognitive function impairment is defined as a score <24 points and such individuals will be excluded from the study
^
71
^. The Geriatric Depression Scale (GDS-15) will be used to screen for depression risk
^
72
^. This scale assigns scores of zero or one to each response, with a score >5 indicates risk of depression
^
72
^. The ability of participants to perform ADLs will be assessed using the Katz Index of Independence in ADLs
^
73
^. This Index assesses six functional activities: bathing, dressing, toileting, transferring, continence and feeding
^
73
^.

**Quality of life**

Quality of life will be assessed using the Short Form (SF)-12 × 2
^®^
^
74
^. This instrument uses twelve questions to assess perceived general health (physical and social function, pain, emotion and mental health)
^
74
^. The physical component score indicates physical health status and the mental component score indicates psychological well-being
^
74
^.

**Feasibility of intervention implementation**

Recruitment and Retention

Recruitment rate will be defined as the percentage of eligible participants who consent to participate in the research study (total number of participants recruited divided by the total number of people screened for eligibility multiplied by 100). Retention rate will be defined as the percentage of participants who start and go on to complete the study intervention. The number of participants who complete the follow-up assessment (T3) will also be recorded. Reasons for study dropout will be recorded.

Adherence to oral nutritional supplement

Participants will be asked to self-report intake of ONS per day using a paper copy ONS recording sheet that provides instructions on how to consume the ONS. Participants will check two tick boxes to indicate they have consumed two ONS on the day of consumption and tick one box if only one ONS is consumed. If they have not completely consumed a bottle, they will be asked to record this for the specific day. Participants will be asked to retain both used and unused ONS bottles; these will be counted at the end of the intervention. Adequate adherence will be defined as consuming an average of 10 out of 14 (71%) ONS per week over the 12-week intervention
^
75
^. Reasons for non-adherence will be recorded.

Adherence to resistance training

Adherence during the supervised RT session will be monitored by the Exercise Instructor who will record attendance, number of repetitions, sets, weight used, and the RPE on the study online recording database. Adequate adherence will be defined as successfully participating in 18 out of 24 sessions (>75%)
^
76
^. Reasons for non-adherence will be recorded.

Acceptability of the oral nutritional supplement

Acceptability of the ONS will be assessed post-intervention with three questions using a 9-point Hedonic scale to evaluate flavour, texture, and overall acceptance
^
77
^. Additionally, four questions will utilise a 5-point Hedonic scale to assess visual appearance, smell, taste, and aftertaste of the ONS
^
77
^. Participants will also respond to a final question regarding their willingness to purchase the protein drink, with options ranging from "would certainly buy" to "would certainly not buy"
^
77
^.

Acceptability of the resistance training programme

A short bespoke questionnaire completed by participants post-intervention will be used to evaluate their perceptions of the RT programme. All questionnaire statements are framed positively, and participants will be asked to rate their agreement with each statement on a five-point Likert scale ranging from “Strongly disagree” to “Strongly agree”. Participants’ responses will be collated and summarised
^
78
^.

### Adverse events

Should an adverse event occur, it will be discussed immediately with the research advisory team ([name]) and participants will be advised to contact their general practitioner as appropriate. As per ethical approval, the occurrence of any unexpected serious adverse event will be reported to the UCD HREC (
[contact]).

### Data management

Personal data will be stored in a password protected university database in compliance with the Data Protection Act 2018
^
79
^. Only the researchers will have access to this information. Each participant will be assigned a study identification number, which will be used to pseudonymise the data collected. All data will be pseudonymised for analysis, enabling the potential re-linking of individual participant data for data checking if necessary. All data will be anonymised after four years. No personal data will be transferred to Nutricia Ireland Ltd as per the signed legal agreement between UCD and Nutricia Ireland. Study data will be made available to researchers upon reasonable request.

### Statistical analysis plan

Statistical analyses will be performed using SPSS Statistics for Windows, version 27 (SPSS Inc., Chicago, Ill., USA) and RStudio (2023.06.2. Posit, PBC) as appropriate. Data cleaning will be conducted prior to analysis.

Demographic data and study primary and secondary outcomes will be described using measures such as mean and standard deviation, median and interquartile range, 95% confidence interval, or count and percentage. Descriptive statistics will also be used to report the feasibility of the intervention. Missing data will not be imputed for the primary analysis.

Data will be analysed using the intention-to-treat approach, wherein all participants who have been randomly allocated to the study intervention
^
80
^ will be included. The between-group and within-group difference at baseline (T1), post-intervention (T2) and 12-weeks post-intervention (T3) in primary and secondary outcomes will be analysed using either parametric or non-parametric, based on the normality of data distribution. The primary outcome is TUG and MNA-FF post-intervention (T2). Further, a mixed between-within linear model will be used to assess group, time, and group x time interaction effects. Between-group linear mixed-model analysis will be used to assess the mean difference in change from baseline to post-intervention. The dependent variables will be TUG and MNA-FF with group (ONS + RT, RT), time (baseline, post-intervention), and the group-by-time interaction as fixed factors; participant ID as a random factor; and baseline values as covariates. Effect sizes (partial eta squared) will be calculated using the Cohen’s d classification (0.01 = small, 0.06 = moderate, 0.14 = large). Variables not normally distributed will be transformed as appropriate. The proportion of participants whose TUG and/or MNA-FF improved or deteriorated post-intervention (T2) will be calculated. The interindividual variability in response to the ONS will be calculated using the Atkinson and Batterham formula
^
81
^.

Using the same approach as above, between-group differences and within-group differences at baseline (T1), post-intervention (T2), and 12 weeks post-intervention (T3) will be analysed for secondary outcomes.

A per-protocol analysis will also be conducted, including participants who adhered to the intervention and have baseline (T1) and post-intervention (T2) measurements
^
82
^.

A p-value of less than 0.05 will be considered statistically significant.

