### Sample size

Study sample size calculation was conducted in G* Power (version 3.1). Based on previous study findings
^
36
^, 15 participants per group are required to detect a mean difference of 3.7 seconds in time to complete TUG with 80% power and significance at p<0.05. Additionally, based on the same findings
^
36
^, 16 participants per group will be needed to detect a mean difference of 1.52 in MNA-FF score between the intervention group and the control group with 80% power and significance at p<0.05. To ensure an adequate sample size to enable per protocol analysis, the sample size was increased to 23 participants per group
^
46
^. This will allow for both intention-to-treat and per-protocol analyses, ensuring rigorous analysis of intervention effectiveness.

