### Randomisation and blinding

On meeting the eligibility criteria, participants will be randomised into either the (i) ONS + RT or (ii) RT only, using a 1:1 ratio by an independent researcher not involved in the POWER study using the Clinical Trial Randomization Tool hosted by the
National Cancer Institute. Eligible participants will be assigned an identification number and then added to the study database. It will not be possible to blind the participant or researchers to the intervention allocation.

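### The protocol plans between-arm significance tests at baseline (T1); they answer no trial question, and unconditional adjustment for T1 should replace them

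*Protocol article*

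**What the plan says.** All the relevant text on analysis is in the protocol article, Statistical analysis plan.

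- Primary and secondary outcomes: "The between-group and within-group difference at baseline (T1), post-intervention (T2) and 12-weeks post-intervention (T3) in primary and secondary outcomes will be analysed". The method follows in the same sentence: these differences "will be analysed using either parametric or non-parametric, based on the normality of data distribution".
- Secondary outcomes, a second time: "between-group differences and within-group differences at baseline (T1), post-intervention (T2), and 12 weeks post-intervention (T3) will be analysed for secondary outcomes".
- Threshold: "A p-value of less than 0.05 will be considered statistically significant". T1 is not exempted.
- Descriptive summaries of the outcomes are planned in a separate, earlier sentence, so the T1 comparison is additional to description.
- A mixed model for TUG and MNA-FF, with baseline and post-intervention as its time levels, includes the baseline value as a covariate. This does not depend on what T1 shows.
- Feasibility outcomes are descriptive only.

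Under Randomisation and blinding, allocation is made "using a 1:1 ratio by an independent researcher not involved in the POWER study", and "It will not be possible to blind the participant or researchers to the intervention allocation". Under Sample size, "the sample size was increased to 23 participants per group".

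**The concern.** Before treatment starts, properly randomised arms differ only by chance. A between-arm test at T1 therefore tests a null hypothesis that the design has already made true, and its p-value bears on no question of the trial.

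Two misreadings follow. A significant T1 result invites doubt about a sound randomisation. A non-significant one invites the view that the arms are balanced, although the test cannot detect imbalances large enough to shift an unadjusted T2 or T3 comparison. The second matters here because the stand-alone parametric or non-parametric comparisons at T2 and T3 carry no stated baseline adjustment.

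The drafting is also loose: a within-group difference has no meaning at a single time point.

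**Working it through.** **Inputs.** 23 per arm (Sample size); alpha 0.05 (Statistical analysis plan), taken as two-sided because sidedness is not stated; outcomes measured at T1 (Table 3 and Study outcomes). The protocol gives no figure for the T1 tests themselves.

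**1. Number of tests.**
- Low count: Table 3 has 11 non-feasibility outcome rows at T1 (2 primary, 9 secondary).
- High count, separate measures: fat in kg and %, muscle in kg and %, weight, BMI, calf and mid-upper-arm circumference (8); protein and energy intake (2); gait speed, grip strength, five-times sit-to-stand, MMSE, GDS-15 and Katz (6); SF-12 physical and mental scores (2). That is 18 secondary measures, and 20 with TUG and MNA-FF.

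**2. Per-test rejection rate under randomisation.** In 20,000 simulated trials with 23 per arm and skewed data, the t-test rejected in 5.2% and the Mann-Whitney test in 5.1%. Rejections occur at the nominal chance rate.

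**3. False positives.** Expected number = 0.05 × k. P(at least one) = 1 − 0.95^k if the tests are independent. Correlated cases were simulated with a common correlation; the documents give none, so these values are assumptions.

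| k | Expected | Independent | Correlated |
|---|---|---|---|
| 11 | 0.05 × 11 = 0.55 | 1 − 0.95^11 = 43% | 38% at 0.3; 31% at 0.5; 18% at 0.8 |
| 20 | 0.05 × 20 = 1.0 | 1 − 0.95^20 = 64% | 59% at 0.2; 48% at 0.4 |

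For correlations up to 0.5 the range is about 30% to 64%. A uniform correlation of 0.8 across measures as different as grip strength and depression score would be extreme.

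**4. Largest observed imbalance that stays non-significant.** With 44 degrees of freedom:

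t(0.975, 44) × √(2/23) = 2.015 × 0.295 = 0.59 SD.

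**5. The same limit in outcome units.** The Sample size section states 15 per group for 3.7 s on TUG and 16 per group for 1.52 points on MNA-FF, at 80% power. No SD is given, so these sizes cannot be reproduced directly. Solving the two-sided two-sample t-test backwards gives the SDs that would yield exactly those sizes:
- TUG: SD 3.36 to 3.49 s, so 0.594 × SD is about 2.0 to 2.1 s, over half of 3.7 s.
- MNA-FF: SD 1.43 to 1.48 points, so 0.594 × SD is about 0.85 to 0.88 points, over half of 1.52.

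These SDs are inferred and may be SDs of change rather than of baseline values. If the sample size calculation was one-sided, the implied SDs are 3.83 to 3.98 s and 1.63 to 1.69 points, and the limits rise to about 2.3 to 2.4 s and 0.97 to 1.00 points.

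**6. How often a sizeable chance imbalance is flagged.** The standard error of a standardised difference is √(2/23) = 0.295, so P(|difference| > 0.4 SD) is about 17.5%. The test rejects in 5% of trials, all of them beyond 0.59 SD. It therefore flags about 0.05 / 0.175 = 29% of imbalances above 0.4 SD and misses the rest.

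**The case against.** The strongest reply is that nothing depends on the T1 tests. No covariate choice, model choice or exclusion is tied to a T1 p-value, and the TUG and MNA-FF model adjusts for baseline whatever T1 shows. Sample size and that model's T2 error rate are unaffected. This stands, and it limits the severity. It does not cover everything: the covariate sentence names only TUG and MNA-FF and only the baseline and post-intervention time points. The secondary outcomes are referred to the same approach, but that does not clearly bring a baseline covariate to them, or to any outcome at T3.

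Second, the sentence may be condensed drafting in which T1 serves mainly as the reference for within-group change. That is plausible for the within-group part. The between-group T1 comparison is nevertheless explicit and appears twice.

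Several stronger readings are tempting but not supported:
- A reader might infer that every significant T1 result must be a false positive. That needs T1 to be measured before allocation is known. The protocol randomises once eligibility is met, screens by telephone, ticks randomisation at T1 in Table 3 and blinds nobody, so the order is not fixed. A T1 difference could then reflect assessment with allocation known, although a significance test would be a poor check for that.
- A reader might infer that a spurious difference will usually appear. The range in the working runs from below to above one half.
- A reader might infer that all secondary outcomes are tested at T1. Feasibility is a secondary outcome, is descriptive only and mostly has no T1 value.
- A reader might quote the test's power against a true T1 difference. Randomisation rules out such a difference; the relevant limit is on the observed one.

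**Conclusion.** The point holds in limited form. The protocol specifies between-arm inferential tests at T1 for the primary and secondary outcomes measured there. A significant result is uninformative if allocation was sound and T1 was measured before allocation was known, and a non-significant result does not show balance. The false-positive range assumes 11 to 20 tests and common correlations of at most 0.5; the 0.59 SD limit assumes a two-sided t-test with 23 analysed per arm. The conversion to seconds and points rests on inferred SDs and is illustrative.

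Severity is minor to moderate. The damage is to reporting and interpretation, and to stand-alone T2 and T3 comparisons that may be left unadjusted on the strength of a reassuring T1 p-value. The documents do not support a claim that the mixed-model T2 analysis of TUG and MNA-FF is compromised by these tests.

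**What to change.** In the Statistical analysis plan:

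1. In both sentences, restrict between-group comparisons to T2 and T3. Keep T1 as the reference point for within-group change; striking T1 out altogether would leave only T2 against T3.
2. State that T1 values are presented by arm with the descriptive summaries already planned, without p-values.
3. State that all between-arm estimates at T2 and T3, primary and secondary, are adjusted for the T1 value of the same outcome, however T1 looks.

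The cost is two edited sentences and two short additions. The T1 values are already collected, so no data, participants or visits are added and the sample size does not change. Expected false positives from this source fall from 0.55 or more to zero.

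### Each T2 primary outcome is tested by an unadjusted two-group test and by a mixed model, both at p<0.05, and neither is named as the primary analysis

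*Protocol article*

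**What the plan says.** All of this stands in the Statistical analysis plan section of the protocol article.

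- **Two-group comparisons.** The sentence that begins "The between-group and within-group difference at baseline (T1" covers T1, T2 and T3 and both primary and secondary outcomes. These differences "will be analysed using either parametric or non-parametric, based on the normality of data distribution". No baseline adjustment is mentioned for them.
- **Primary time point.** The next sentence fixes it: "The primary outcome is TUG and MNA-FF post-intervention (T2").
- **Mixed model.** The text continues: "Further, a mixed between-within linear model will be used to assess group, time, and group x time interaction effects". Then: "Between-group linear mixed-model analysis will be used to assess the mean difference in change from baseline to post-intervention". TUG and MNA-FF are the dependent variables, "with group (ONS + RT, RT), time (baseline, post-intervention), and the group-by-time interaction as fixed factors", with participant as a random factor and the baseline value as a covariate.
- **Non-normal data.** After the model: "Variables not normally distributed will be transformed as appropriate".
- **Threshold.** One rule covers everything: "A p-value of less than 0.05 will be considered statistically significant".

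The term primary analysis occurs in this section, in the sentence on missing data, and again in the Discussion, in the paragraph on limitations. The first place gives no method. The second gives only the comparison of ONS + RT with RT alone.

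**The concern.** The same hypothesis, no difference between arms in TUG (or MNA-FF) at T2, receives two p-values. They come from different contrasts: an unadjusted comparison of T2 values, and a comparison of change that uses baseline. With 46 participants the two can easily disagree, and the text has no rule for that case.

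The wording does not settle which one leads. The primary outcome is named straight after the two-group test, and the model is then added as a further step, which points to the simple test. The model is the one specified in detail, which points the other way. Two careful readers could report different headline results from the same data and both cite the plan.

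Two things are at stake. One is the false-positive rate if either result may be claimed. The other is power, if the unadjusted test turns out to be the headline. The choice also affects what is estimated, because a rank test and a mean difference answer different questions.

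The section also lists a between-group comparison at T1. Under randomisation the null hypothesis is true there by design, so a p-value tells the reader nothing about the treatment.

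**Working it through.** **Inputs from the protocol article.** 23 per arm (Sample size); 1:1 allocation (Randomisation and blinding); threshold 0.05 per test (Statistical analysis plan).

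**Assumptions.** Tests are two-sided; the text does not say. The correlation ρ between baseline and T2 is not given, so a range of 0.3–0.9 is used, with equal SDs at the two times.

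**The plan's own figures.** The Sample size section gives 15 per group for 3.7 s in TUG and 16 per group for 1.52 points in MNA-FF, at 80% power, without SDs. A two-sided t-test then implies standardised effects of about 1.06 (SD about 3.49 s) and 1.02 (SD about 1.48). These figures can be neither confirmed nor refuted, and nothing below depends on them.

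**Step 1: each analysis alone.** Null simulation, 23 per arm, 10,000 runs per setting, normal and skewed data, ρ from 0.3 to 0.95. Shapiro–Wilk chose between t-test and Mann–Whitney at T2.

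| Analysis alone | Rejection rate |
|---|---|
| Normality-chosen T2 test | 4.5–5.7% |
| Change test | 4.7–5.5% |
| ANCOVA at T2 | 4.4–5.7% |

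Each stays near 5%, so the normality check is not the source of any inflation.

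**Step 2: either analysis significant.** Under the null, P(either) = 0.05 + 0.05 − P(both). P(both) depends on the correlation between the two test statistics:

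- T2 test and group-by-time change test: √((1−ρ)/2)
- T2 test and baseline-adjusted ANCOVA: √(1−ρ²)

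Worked example at ρ = 0.5. For the change test the correlation is √(0.5/2) = 0.50; the bivariate normal gives P(both) = 0.0093, so P(either) = 0.1000 − 0.0093 = 0.0907. For ANCOVA the correlation is √0.75 = 0.866; P(both) = 0.0266, so P(either) = 0.0734.

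| ρ | T2 test or change test | T2 test or ANCOVA |
|---|---|---|
| 0.3 | 8.8% | 6.4% |
| 0.5 | 9.1% | 7.3% |
| 0.7 | 9.4% | 8.3% |
| 0.9 | 9.6% | 9.2% |

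The ceiling for two independent tests is 1 − 0.95² = 9.75%. Over ρ = 0.3–0.9, the simulation with the Shapiro–Wilk step gave 8.3–10.5% for the first column and 5.9–9.8% for the second, consistent with the analytic values.

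**Step 3: the model as literally worded.** Baseline appears both as an outcome row (time has a baseline level) and as a covariate. This pushes the estimated participant variance towards zero. In simulation that model alone rejected in 5.2–8.1% of null trials. This is why the fix below keeps baseline out of the outcome rows.

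**Step 4: power.** The illustrative effect is 0.845 SD, chosen because the unadjusted T2 test has 80% power for it at 23 per arm. It is not a figure from the documents. Noncentrality is d × √(23/2), and baseline adjustment divides d by √(1−ρ²).

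- Unadjusted: 0.845 × √11.5 = 2.87, 44 df: power 80%.
- Adjusted, ρ = 0.5: 0.845/√0.75 = 0.976; 0.976 × √11.5 = 3.31, 43 df: power about 90%.
- Adjusted, ρ = 0.7: 0.845/√0.51 = 1.183; 1.183 × √11.5 = 4.01, 43 df: power about 97.5%.

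**The case against.** The strongest reply is that the inflation is conditional. The protocol nowhere says that success may be claimed on either analysis; it only fails to exclude it. That stands, and the figures are therefore stated as what would follow if either could be claimed. A flat statement that the error rate nearly doubles would go too far. It needs that condition and the group-by-time reading of the model; under ANCOVA with a modest correlation the rate is nearer 6–7%.

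The power argument can also be answered in part. The plan already contains a model with baseline as a covariate, so power is lost only if the unadjusted test becomes the headline. That is correct, and it is a reason to settle the order now.

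Four stronger readings are tempting, and the documents do not support them:

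- *The normality check inflates the error rate.* It does not; the chosen test alone stays near 5%.
- *The instructions for non-normal data contradict each other.* The non-parametric option governs the two-group comparisons, and the transformation sentence follows the linear model. The two are compatible, though loosely worded.
- *The analyst is unblinded when choosing.* The Randomisation and blinding section says that participants and researchers cannot be blinded to allocation. It does not say who analyses the data or whether arms are coded.
- *The error compounds across TUG and MNA-FF.* Multiplicity over two outcomes is a separate question, and any figure for it would need an assumption about their dependence.

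Nor is there any sign that within-group results will be used to claim a difference between arms. The Discussion gives a purpose for the time effects: interpretation against minimal clinically important differences.

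A separate analysis plan might name the primary method. But this section already prescribes two tests of the same outcome at the same threshold, so the issue is what it states, not detail left out.

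**Conclusion.** The point holds in conditional form. For TUG and MNA-FF at T2 the plan prescribes an unadjusted normality-chosen test and a mixed model with baseline as a covariate, each at p<0.05, and designates neither as primary. If either result could be claimed, the false-positive rate per outcome is about 9–10% under the group-by-time reading and about 6–9% under the ANCOVA reading, against 5% for one named analysis.

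That the two analyses are both prescribed and left unranked is certain from the text. The size is less certain, because it rests on an assumed ρ of 0.3–0.9, two-sided tests, and which reading of the model is intended. The power gap (80% against about 90% or 97.5%) is illustrative, but its direction does not depend on the effect chosen: for any material baseline correlation, the unadjusted T2 comparison is the weaker of the two. This should be changed before analysis.

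**What to change.** 1. Name one primary analysis for each outcome: the baseline-adjusted difference between arms at T2 on the original scale, with the baseline value as a covariate and not also as an outcome row.
2. Prespecify an analysis of log(TUG) as the sensitivity analysis for skew.
3. Label the two-group T2 test as supportive, and within-group results as supportive or descriptive.
4. Drop the between-group significance tests at T1 and describe baseline by arm without p-values.

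The cost is rewording. No participants, visits or measurements are added, and fewer tests are run. The small downside is that there is no separate non-parametric headline p-value.

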^. Older adults residing in the Northern Hemisphere should also take a daily vitamin D supplement (15 µg for healthy older adults and 20 µg for home bound older adults)
^
19,
31–
33
^. Providing ONS fortified with whey protein, leucine and vitamin D has shown promise in improving health-related outcomes
^
34,
35
^ while such ONS combined with RT in older adults with sarcopenia have shown positive effects on muscle strength, body composition and physical function
^
34
^.

Older adults with sarcopenia, undergoing physical rehabilitation, demonstrated improvements in physical function [Timed Up & Go (TUG) and gait speed) and nutritional status (Mini-Nutritional Assessment-Full Form (MNA-FF)] following 8 weeks of ONS enriched with leucine and vitamin D and supervised RT compared to an isocaloric placebo supplementation and supervised RT
^
36
^. These findings demonstrate the added benefits of nutritional supplementation to improve outcomes of an exercise programme in hospitalised older adults. However, whether similar effects are observed in older adults receiving supportive home care is unknown. Older adults with sarcopenia are recommended to perform at least two RT sessions per week
^
18,
37
^. Given that a number of studies indicate older adults are less likely to engage in exercise programmes for varying reasons
^
38,
39
^, supervised exercise programmes delivered via an online platform are worth considering
^
40,
41
^. Online platforms such as Zoom provide a potential and accessible solution for older adults who have mobility and/or transportation limitations
^
41–
43
^. Providing a supervised and consistent programme can improve adherence
^
44
^ plus the group-based aspect can provide a social element
^
41
^. Recent studies indicate overall acceptability of online exercise programmes among healthy older adults
^
41,
44
^.

Hence, the aim of this study is to test the effectiveness of a new whey protein ONS enriched with leucine and vitamin D (Fortimel Advanced, Nutricia) combined with an online RT programme versus the RT programme alone on the physical function and nutritional status of older adults receiving supportive home care who are at risk of sarcopenia. The primary outcomes of the study are 1) physical function as measured by the TUG and 2) nutritional status as measured by the MNA-FF.

Trial registration:
NCT05688956; registered December 2022.

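### Two primary outcomes are each tested at p<0.05 with no success rule; if either one suffices, the chance of a false primary finding is up to about 10%

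*Protocol article*

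**What the plan says.** The Background of the Protocol article sets out two primary outcomes: "The primary outcomes of the study are 1) physical function as measured by the TUG and 2) nutritional status as measured by the MNA-FF". The Study outcomes section repeats both, and the Statistical analysis plan section fixes the time point: "The primary outcome is TUG and MNA-FF post-intervention (T2".

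The Sample size section treats them one at a time, each at the full 5% level:

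- TUG: "15 participants per group are required to detect a mean difference of 3.7 seconds in time to complete TUG with 80% power and significance", the threshold being p<0.05.
- MNA-FF: "16 participants per group will be needed to detect a mean difference of 1.52 in MNA-FF score", again with 80% power and p<0.05.

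The number is then raised to 23 per group (46 in total) so that a per-protocol analysis is possible. The effects come from an earlier study ("Based on previous study findings"), and no standard deviation is given.

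In the Statistical analysis plan section, each outcome is a dependent variable in its own linear mixed model. The section has one significance rule: "A p-value of less than 0.05 will be considered statistically significant". The article gives no order of testing and no split of the 5%. It does not say that both outcomes must be significant, or that one is enough.

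**The concern.** A trial with two primary outcomes needs a rule that turns two p-values into one conclusion. Without one, a result with one significant and one null primary outcome can be presented as success or as failure after the data are seen. That matters here for three reasons. The stated aim is to test effectiveness. Neither participants nor researchers are blinded (Randomisation and blinding). The results are reported to the funder, which is also named as the maker of the supplement.

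The stated design figures do not settle the matter under either rule. If one significant outcome is enough, two tests at 5% do not give a 5% error rate for the claim. If both are needed, the error rate is safe, but 80% is the power for each outcome alone and not for the pair.

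**Working it through.** **Inputs from the Protocol article.** Two primary outcomes at T2; threshold 0.05 for each; TUG 15 per group for 3.7 s; MNA-FF 16 per group for 1.52 points; 80% power each; 23 per group planned; 1:1 allocation.

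**Inputs assumed.** Tests are two-sided (the article does not say). Standardised effects are back-solved, since no SD is given. The correlation between the two test statistics is not given, so a range is shown.

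**1. Error if either outcome suffices.** Under independence:

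1 − (1 − 0.05)² = 1 − 0.9025 = 0.0975.

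The upper bound for any dependence is 0.05 + 0.05 = 0.10. For correlated two-sided tests (bivariate normal, critical value 1.96):

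| Correlation | Either direction | Benefit only |
|---|---|---|
| 0 | 9.75% | 4.9% |
| 0.2 | 9.6% | 4.8% |
| 0.5 | 9.1% | 4.5% |
| 0.7 | 8.3% | 4.2% |
| 0.9 | 7.0% | 3.5% |

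The single-test reference values are 5% and 2.5%.

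**2. The plan's own sample sizes.** The stated 15 and 16 cannot be reproduced without an SD, so they are inverted. Power of a two-sample t-test comes from the noncentral t distribution with 2n − 2 degrees of freedom and noncentrality d√(n/2). Because n is rounded up, the stated n is consistent with a range of d: at the low end power is exactly 80% at the stated n, and at the high end it is 80% at one fewer per group.

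- TUG, n = 15: d = 1.06 to 1.10, so SD = 3.7/d = 3.49 to 3.36 s.
- MNA-FF, n = 16: d = 1.02 to 1.06, so SD = 1.52/d = 1.48 to 1.43 points.

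**3. Either suffices, with control at 0.025 for the first test.** The same effects at a two-sided level of 0.025:

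| | n per group for 80% | Power at 23 per group |
|---|---|---|
| TUG | 18–19 | 89–92% |
| MNA-FF | 19–20 | 87–89% |

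Under Holm's procedure these are lower limits for each outcome, because the second test may use 0.05. With 0.025 for each, family-wise error is 1 − 0.975² = 4.94% under independence and at most 5% in general.

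If the original sizing was one-sided at 0.05, the same calculation with one-sided tests at 0.025 needs 18–20 (TUG) and 20–21 (MNA-FF) per group. Power at 23 is then 87–89% and 85–87%.

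**4. Both required.** Family-wise error is at most 5%. Joint power at level 0.05 each, using the lower-end effects:

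- 23 per group: 0.940 × 0.924 = 0.87 under independence. Whatever the dependence, it lies between 0.940 + 0.924 − 1 = 0.86 and 0.92.
- 20 evaluable per group: 0.904 × 0.884 = 0.80 under independence.

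**The case against.** The strongest reply is that the 10% figure is conditional. The article never says that one significant outcome is enough. Its aim is worded as physical function together with nutritional status, which is also compatible with requiring both, or with answering two separate questions. On the both-required reading the error rate is at most 5%. This stands: a reader might infer that the trial simply runs at a 10% false-positive rate, and the article does not support that. What it supports is an undefined rule, with an error of up to about 10% on one natural reading.

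The 9.75% also counts rejections in either direction. For false claims that the supplement helps, the comparison is about 4.9% against 2.5%. The doubling remains, but from a lower base.

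A reader might also take joint power at 16 per group and conclude that requiring both outcomes is unaffordable. That is the wrong sample size: 16 is the calculated minimum for MNA-FF alone, and 23 are planned. The article says the increase was made to allow a per-protocol analysis, but it does not state 16 as a per-protocol target.

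The point might be stretched to the secondary outcomes, which share the 0.05 threshold. The article does not say that they will carry confirmatory claims, and reporting them unadjusted is common practice, so that extension is not made here.

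Finally, one could say that the rule belongs in a separate analysis plan. This answers only part of the point. The article's own Statistical analysis plan section fixes the threshold, and its Sample size section uses the full 5% twice. A later document that split the 5% would have to depart from both.

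**Conclusion.** The point holds in conditional form. Two primary outcomes are each sized and tested at 0.05, and no rule says what counts as success. If significance on either one counts, the two-sided family-wise error is up to about 10%: 9.75% under independence and still 8.3% at a correlation of 0.7. It exceeds 5% at any correlation below 1. If both must be significant, the error is controlled, but the stated 80% does not describe the power of that claim.

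The error rates depend only on the number of tests, the threshold and the unknown correlation. The power and sample-size figures are less firm: they rest on a t-test, complete data and effects back-solved from the stated 15 and 16 per group, because the article gives no SD. On those assumptions the planned 23 per group can support either rule.

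**What to change.** State the success rule before the data are analysed. Which rule is right depends on the claim the investigators intend to make.

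- **If either outcome can support the claim:** test the pair with Holm's procedure, comparing the smaller p-value with 0.025 and, if that is significant, the other with 0.05. Restate the sample size at 0.025, giving the SDs used. On the assumptions above this means about 18–19 per group for TUG and 19–20 for MNA-FF, with about 89–92% and 87–89% power at 23 per group and complete data.
- **If both are required:** say so, keep 0.05 for each, and replace the two separate 80% statements with joint power. On the lower-end effects and under independence this is about 87% at 23 per group and about 80% at 20 evaluable per group.

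The cost is a few sentences and, under Holm, slightly lower stated power for each outcome. No extra participants are needed.
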